## Abstract

**Aims:**

The Türkiye Heart Failure (TURK‐HF) registry aims to identify the sociodemographic and clinical characteristics, management strategies, and outcomes of patients with heart failure (HF) and to assess the implementation of evidence‐based HF therapies in Türkiye.

**Methods:**

The TURK‐HF registry is a national, multicenter, prospective, observational study of unselected patients with HF regardless of ejection fraction. A total of 46 investigators from 38 centers in 22 cities across Türkiye participated in the registry. The study investigators will gain access to the electronic case report form via www.turkhf.com website using their usernames and passwords. The baseline assessment of the patients will include sociodemographic data, primary care access information, frailty assessment, health‐related quality of life questionnaire, HF‐related information, medical history and comorbidities, physical examination findings, electrocardiographic and echocardiographic data, H_2_FPEF score calculation, laboratory results, and medical and device‐based HF therapies. The management strategies and potential complications of patients hospitalized with acute HF will be systematically documented. Follow‐up data will be collected at regular outpatient visits every 6 months with a margin of error of 1 month. The clinical endpoints of the TURK‐HF registry were cardiovascular or all‐cause mortality, HF‐related hospitalizations, clinician‐interpreted outcomes, patient‐reported outcomes, and surrogate endpoints, either alone or in combination. The TURK‐HF registry was registered at ClinicalTrials.gov (ID: NCT06707220).

**Conclusion:**

The TURK‐HF registry offers comprehensive and distinctive insights into contemporary HF clinical characteristics, diagnostic methods, treatments, and outcomes. This registry has the potential to influence implementation strategies, clinical research, and public policies across Türkiye.

## Introduction

1

Heart failure (HF) is a public health concern associated with higher rates of hospitalization, mortality, and healthcare resource utilization [1]. The incidence of HF in Europe is approximately five per 1000 person‐years in adults, with a prevalence of HF estimated to be between 1% and 2% of the population [2]. However, the prevalence of HF is predicted to rise due to the aging of the population, improved survival rates after myocardial infarction and cancer, advances in pharmacological and device‐based HF therapies, and the greater utilization of heart transplantation over the last decades [1]. Despite these advances, the prognosis of HF remains worse than that of many cancer types, with a 5‐year mortality rate varying from 45% to 60% in adult patients [3].

The proposed terminology based on left ventricular ejection fraction (LVEF) measurement defines “heart failure with reduced ejection fraction” (HFrEF) as LVEF of ≤ 40%, “heart failure with mildly‐reduced ejection fraction” (HFmrEF) as LVEF of 41%–49%, and “heart failure with preserved ejection fraction” (HFpEF) as LVEF ≥ 50% [2]. The main rationale for this terminology is based on clinical trials that have demonstrated beneficial outcomes in patients with HFrEF. Currently, guideline‐directed medical therapies (GDMT), comprising renin‐angiotensin system (RAS) inhibitors, β‐blockers, mineralocorticoid receptor antagonists (MRAs), and sodium−glucose cotransporter‐2 (SGLT‐2) inhibitors, are recommended for patients with HFrEF to reduce the risk of HF hospitalization and death [1, 2]. Notwithstanding compelling evidence from randomized controlled trials and recommendations in current guidelines, the utilization of GDMT among patients with HFrEF remains suboptimal in routine clinical practice [4]. While registry‐based cohort studies have identified numerous patient‐, physician‐, and healthcare system‐related factors associated with the non‐use of GDMT, the discrepancy between current guidelines and clinical practice has not yet been fully elucidated [5, 6].

In contrast, HFpEF is distinct from HFrEF and represents a heterogeneous clinical syndrome. There is a lack of knowledge regarding the pathophysiological mechanisms, comorbidity burden, and phenotypes of HFpEF [7]. Consequently, our understanding of this complex disease remains limited, and the diagnosis and/or treatment of patients with HFpEF remains a significant challenge. In contrast to patients with HFrEF, treatment options for patients with HFpEF are limited. Historically, numerous randomized clinical trials encompassing RAS inhibitors, β‐blockers, and MRAs have failed to show efficacy in patients with HFpEF [1, 2]. In recent years, several promising studies have been conducted. The results of phase 3 clinical trials with SGLT‐2 inhibitors and finerenone have demonstrated favorable outcomes in patients with HFmrEF and/or HFpEF [8, 9, 10]. However, there are still limited real‐world data on the clinical phenotypes and comorbidity burden in patients with HFpEF and the prognostic impact of these novel treatments.

Acute HF is characterized by the sudden onset of symptoms, either de novo HF or due to the worsening of previously diagnosed HF (WHF) [1, 2]. The term WHF is used to describe the progression of disease in patients with chronic HF that requires hospitalization or unplanned emergency department visits. WHF is recognized as an acute deterioration phase in the natural course of the disease, indicating poor prognosis [11]. Despite its clinical importance, WHF remains inadequately defined, and its management remains challenging. Current WHF data are obtained from randomized controlled trials with a highly selected HF population. Although the prognostic significance of WHF events during the course of the disease is known, there is a paucity of data on the definition, management, and outcomes of WHF in real‐world patients.

A comprehensive understanding of the sociodemographic, clinical, and biological characteristics of patients with HF in real‐world settings is essential for developing novel strategies to improve patient outcomes. Identifying the barriers to GDMT implementation in a real‐world setting is critical for decreasing the risk of HF hospitalization and mortality [1, 2]. A comprehensive and well‐designed HF registry can determine the clinical characteristics of patients with HF, identify patient‐, physician‐, and healthcare system‐related factors for the non‐use of evidence‐based therapies, and improve the implementation of GDMT [12]. It should be noted that the number of HF registries that enroll patients with de novo HF, chronic HF (outpatients), and acute HF (hospitalized or treated in the emergency department) in all three relevant EF categories (HFrEF, HFmrEF, and HFpEF) is limited. Furthermore, only a few registries have assessed the detailed aspects of guideline adherence, treatment decisions, and both in‐hospital and long‐term outcomes of these patients. Therefore, the Türkiye Heart Failure (TURK‐HF) registry was designed to address this knowledge gap regarding the identification, management, and long‐term prognosis of patients with HF in a real‐world setting. The registry also aimed to document barriers to externalizing current guidelines for routine patient care in the country.

## Methods

2

### Design

2.1

The TURK‐HF registry is a national, multicenter, prospective, observational study of unselected patients with HF, regardless of LVEF (HFrEF, HFmrEF, or HFpEF), who presented with de novo, chronic, or acute HF requiring hospitalization and/or emergency department admission. This study was approved by the ethics committee (project no. KA23/429–E‐91694447‐604.01‐336905) and will be conducted according to the principles of the Declaration of Helsinki. All patients will provide written informed consent for participation. The TURK‐HF registry was registered at ClinicalTrials.gov (ID: NCT06707220).

### Study Sites and Participant Physicians

2.2

The TURK‐HF registry will be conducted in seven distinct geographical regions in Türkiye. The study sites were identified according to the Nomenclature of Territorial Units for Statistics (NUTS) Level 1 classification system to reflect the population distribution of geographical regions [13]. Detailed data on the cities, NUTS regions, and study sites are presented in Table 1 and Figure 1. To reflect the characteristics of health providers, the study sites were selected based on the projected distribution of health provider subgroups, as presented in the Health Statistics Yearbook [14]. The participant physicians were offered participation by the project coordinator. It was made clear that participation was voluntary and that no financial compensation would be provided for participation. A total of 46 investigators from 38 centers (16 university hospitals, 13 education and research hospitals or city hospitals, 4 state hospitals, and 5 private hospitals) in 22 cities across Türkiye participated in the study (Table 1 and Figure 1). The diagnosis of HF, initiation, up‐titration, and maintenance of HF treatments, disease management, and treatment‐related adverse events and complications are beyond the scope of this registry and are the responsibility of the participating physicians.

**Table 1 clc70353-tbl-0001:** Nomenclature of Territorial Units for Statistics (NUTS) Level 1 regions, cities, and study sites of the TURK‐HF registry.

NUTS Level 1 region	City	Study site
Aegean (TR3)	Izmir	Baskent University, Faculty of Medicine, Department of Cardiology
	Izmir	Medicana International Izmir Hospital, Department of Cardiology
	Izmir	Izmir University of Economics, Faculty of Medicine, Department of Cardiology
	Izmir	Ege University, Faculty of Medicine, Department of Public Health
	Kütahya	Kutahya Health Sciences University, Faculty of Medicine, Department of Cardiology
	Manisa	Manisa Celal Bayar University, Department of Cardiology, Manisa
	Manisa	Manisa City Hospital, Department of Cardiology, Manisa
	Manisa	Akhisar Mustafa Kirazoglu State Hospital, Department of Cardiology, Manisa
	Denizli	Pamukkale University, Department of Cardiology, Denizli
Istanbul (TR1)	Istanbul	Istanbul University‐Cerrahpasa Institute of Cardiology, Department of Cardiology
	Istanbul	Bakirkoy [name] Training and Research Hospital, Department of Cardiology
	Istanbul	[name] Training and Research Hospital, Department of Cardiology

**Figure 1 clc70353-fig-0001:**
[figure not shown]
Geographical distribution of 22 cities in Türkiye that participated in the TURK‐HF registry.

### Study Population

2.3

The only inclusion criterion for the TURK‐HF registry was the presence of HF as determined by the participating physician. The exclusion criteria were age < 18 years and refusal to provide informed consent for registry participation. All patients will be eligible for enrollment, regardless of LVEF (HFrEF, HFmrEF, or HFpEF) or whether they have de novo or chronic HF. All patients will be enrolled in the study, regardless of their clinical status. This encompasses both those presenting for a non‐urgent outpatient visit with stable signs and symptoms and those requiring urgent care for WHF. The objective of this approach was to ensure the representativeness of the study population to the source population to generalize the aim of generalizability of data and externally validate the registry data. WHF is defined as worsening symptoms and signs of HF in patients with chronic HF, requiring hospitalization and/or intravenous diuretic therapy [11]. All study participants provided written informed consent.

### Data Capture, Storage, Security, and Quality Management

2.4

The TURK‐HF registry data will be collected using an electronic case report form (e‐CRF) integrated into an electronic data capture system. The e‐CRF application was developed using the PHP application development language and ran on the Oracle MySQL database. The application is hosted on the service provider's cloud servers in a data center provided by a third party. Daily backups are created in accordance with the backup, restore, and disaster recovery procedures. The application is web‐based and accessible to assigned users with different authorization levels. The study investigators will gain access to the e‐CRF via the www.turkhf.com website using their username and password. Participant physicians who enter data belonging to the centers can only access the data they have entered. User management, access to reports, and authority to view all patient data belong to the user with the administrator role. To guarantee the protection of personal data in Türkiye, the Personal Data Protection Regulation (Law No. 6698) was established [15]. For this purpose, the data collected from patients will be pseudonymized, which means that the personal data cannot be attributed to any specific person without additional information. The data were stored in a centralized registry database that was accessible only to authorized personnel and protected by individual passwords.

### Baseline Clinical Assessment of Patients

2.5

The baseline assessment of patients will include sociodemographic data, primary care access information, frailty assessment, health‐related quality of life (HRQoL) questionnaire, HF‐related information, medical history and comorbidities, physical examination findings, electrocardiographic and echocardiographic data, H_2_FPEF score calculation for patients with HFpEF, laboratory results, and medical and device‐based HF therapies (Figure 2).

**Figure 2 clc70353-fig-0002:**
[figure not shown]
Baseline and follow‐up data elements and time points for patients with chronic heart failure (outpatients) and acute heart failure (hospitalized patients). *Follow‐up data will be collected at regular outpatient visits every 6 months, with a margin of error of 1 month, or via telephone interviews if the patient is not eligible for outpatient visits. **The clinical endpoints of the TURK‐HF registry were cardiovascular or all‐cause mortality, heart failure‐related hospitalizations, clinician‐interpreted outcomes (e.g., New York Heart Association functional class), patient‐reported outcomes (e.g., health‐related quality of life), and surrogate endpoints (e.g., N‐terminal pro‐brain natriuretic peptide levels), either alone or in combination.

#### Sociodemographic Data

2.5.1

To determine the socio‐economic status (SES) and health inequalities, detailed data will be obtained on age, sex, marital status, urban or rural living, housing conditions and household income, education level, and employment status [16]. A detailed approach was adopted to ascertain the SES of individuals in the TURK‐HF Registry. For this purpose, we will question the age, sex, marital status (married or living together, divorced or separated, partner died, or never married), living area (urban or rural), and living conditions (living alone, living only with a partner, living with children and/or grandchildren, or living in a nursing home) of the participants. We classified the education level as no formal education, incomplete primary education, completed primary or secondary education, completed high school, and university graduate. The employment status of the participants was derived from their responses to two questions regarding employment status and profession. We used the classification system of [name], a Turkish economist, for employment status as follows: an employer with ≥ 10 employees, an employer with 3–9 employees, an employer with ≤ 2 employees, a professional, a white‐collared or office worker, a blue‐collared or skilled employee, a retired individual, an unskilled worker, a farm worker, a marginal worker, an unemployed individual, and a housewife [16]. A series of additional inquiries were posed to retired participants to ascertain their employment status and profession before retirement, determine whether they were still employed after retirement, and, if so, what position they held. Unemployment status does not accurately reflect the real socioeconomic situation of housewives; thus, we asked additional questions about the employment status and profession of the person who contributed the most to the household income of housewives. The participants were asked to choose from extremely poor, poor, fair, high, and extremely high household incomes. Participants were invited to provide information regarding the employment status and profession of their parents and their household income during their period of residence with them. Furthermore, patients will be surveyed using the World Values Survey questionnaire to evaluate their self‐reported health and happiness [17].

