#### Physical Examination, Electrocardiography, Echocardiography, and Laboratory Data

2.5.6

Physical examination findings (systolic and diastolic blood pressure, heart rate, height, and weight) of the registry participants will be assessed during the baseline visit. The patients' body mass index will be calculated automatically using an e‐CRF system. Electrocardiographic data, including heart rhythm (normal sinus rhythm, atrial fibrillation or flutter, pacemaker rhythm, or others), presence and type of bundle branch block, and QRS duration; echocardiographic data, including LVEF, left atrium diameter, mitral E/e' ratio, tricuspid regurgitation velocity, estimated systolic pulmonary artery pressure, tricuspid annular plane systolic excursion, and the presence of valvular abnormalities; and laboratory results, including fasting blood glucose, HbA1c, hemoglobin, serum creatinine, sodium, and potassium, alanine aminotransferase, brain natriuretic peptide or N‐terminal pro‐b‐type natriuretic peptide, thyroid stimulant hormone, uric acid, ferritin, transferrin saturation, cancer antigen 125, and urine albumin‐creatinine ratio, will be registered during the first patient visit. The patient's creatinine clearance will be calculated automatically by the e‐CRF system using the Cockcroft−Gault formula [28].

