## Discussion

3

The TURK‐HF registry will be the first national, large‐scale, multicenter, prospective, and observational study comprising outpatients and hospitalized patients with HF, irrespective of their LVEF, conducted in Türkiye. The primary goal of the present registry is to determine the epidemiology, sociodemographic and clinical characteristics, diagnostic approaches, management strategies, and long‐term prognosis of patients with HF in a real‐world setting. The six fundamental research questions that the TURK‐HF registry aimed to answer are as follows: (i) the impact of SES on the utilization of GDMT and prognosis in patients with HF; (ii) the temporal changes in frailty and HRQoL and its association with subsequent prognosis; (iii) diagnostic approaches, algorithms, and scoring systems for patients with HFpEF; (iv) the comorbidity burden in patients with HFpEF and the phenotypes of HFpEF; (v) the patient, physician, and healthcare system‐related barriers for the suboptimal use of evidence‐based therapies, its prognostic impact, and the strategies to improve the implementation of GDMT; and (vi) in‐hospital management strategies, complications, and prognosis in patients with acute HF.

Previous studies conducted in Western countries have demonstrated that patients with low SES have a higher incidence and prevalence of HF [34, 35]. A published post hoc analysis of the study reported worse clinical outcomes in patients with lower SES [36]. However, the socioeconomic structure of Türkiye differs from that of European, American, and Far Eastern countries, and national data from Türkiye on the impact of SES on the use of GDMT and prognosis in patients with HF are lacking. Therefore, the collection of current data from the real‐life registry is crucial to understand the actual relationship between SES and access to healthcare, receiving GDMT, and prognosis in patients with HF in Türkiye. For the first time, the TURK‐HF registry used the analytic approach described by Boratav to determine the SES of the study participants [16]. As Boratav posits, social classes and individuals' SES are delineated by their relationships within the production process, which are predicated on the control over the means of production. Thus, the TURK‐HF registry design will allow us to obtain detailed data on the participants' control over the means of production, in addition to classical SES variables, including marital status, living area, and education level.

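### The printed living-conditions options are not exhaustive: patients living with parents, siblings, other relatives or a carer, with or without a partner, fit none of them

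*Protocol article*

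**What the plan says.** Section 2.5.1 (Sociodemographic Data) introduces the item as part of the SES assessment: "A detailed approach was adopted to ascertain the SES of individuals in the" registry. Living conditions take one of four values: "living alone, living only with a partner, living with children and/or grandchildren, or living in a nursing home". Marital status is a separate item with its own four values: "married or living together, divorced or separated, partner died, or never married".

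Section 2.3 (Study Population) sets very wide entry: "The exclusion criteria were age < 18 years and refusal to provide informed consent for registry participation". Any consenting adult with physician-determined heart failure can enter, whatever the household.

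The Discussion lists as research question (i) "the impact of SES on the utilization of GDMT and prognosis in patients with HF". When it gives examples of classical SES variables it writes "including marital status, living area, and education level"; living conditions are not among those examples.

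Section 2.8 (Current Situation) reports 1240 patients registered in the first 6 months, with baseline results to be announced after one year of enrollment.

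**The concern.** A single-choice item needs options that cover every eligible patient. This list reads as closed: four options, the last joined by an *or*, with no catch-all. Some ordinary adult households fall outside it. Three of the four marital-status values describe people without a current partner, so the registry expects patients for whom the partner option is unavailable. Those who also have no children or grandchildren at home, but do not live alone or in a nursing home, have nowhere to go. The word *only* in the partner option leaves out a second group: couples who share the home with a parent, sibling or other relative.

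A site that meets such a patient has three choices, each of which damages the variable:

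- Code the patient as living alone, which puts someone with company at home into the group without it.
- Use a family, partner or nursing-home code, which contaminates that category.
- Leave the item blank, which loses the value and may do so selectively.

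No rule is printed for choosing among these, so 38 centers may choose differently. Section 2.6 (Follow-Up Visits) does not list sociodemographic items among the data collected later, so a wrong baseline entry is unlikely to be corrected by routine follow-up.

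**Working it through.** The plan gives no figure on this point, so there is none to reproduce. The check is one of coverage, followed by an illustration of size.

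**Step 1: coverage of the printed list.**

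| Household of an eligible adult | Alone | Only with partner | Children and/or grandchildren | Nursing home |
|---|---|---|---|---|
| Unpartnered, with parents | no | no | no | no |
| Unpartnered, with siblings or other relatives | no | no | no | no |
| Unpartnered, with a live-in carer | no | no | no | no |
| Partner plus parent or other relative, no children at home | no | no | no | no |

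All four households are admissible under section 2.3, and none has a matching option.

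**Step 2: is the missing catch-all just the article's style?** Elsewhere the article prints a residual option where one exists. Heart rhythm in section 2.5.6 reads "normal sinus rhythm, atrial fibrillation or flutter, pacemaker rhythm, or others", and the cause-of-death lists in section 2.5.9 also end with an open category. This makes it plausible that the four options are the whole list, but does not prove it. The 12-value employment list in section 2.5.1 prints no residual option either.

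**Step 3: how many patients.** The documents give no share for unlisted households. Let *u* be that share, assumed to be 2%, 5% or 10%. Among the 1240 registered:

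- 1240 × 0.02 = 24.8, about 25
- 1240 × 0.05 = 62
- 1240 × 0.10 = 124

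**Step 4: effect on one possible comparison.** The article defines no comparison of patients living alone with all others; this one serves only to show how the answer depends on site behavior. Let *a* be the true share living alone (assumed 10% or 20%) and *m* the fraction of unlisted patients coded as alone. Assume that unlisted patients carry the same risk as others who do not live alone. Then

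observed / true risk difference = *a* / (*a* + *u* × *m*)

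For example, with *a* = 0.10, *u* = 0.05 and *m* = 1: 0.10 / (0.10 + 0.05) = 0.67.

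| *u* | *m* = 0 | *m* = 0.5 (*a* = 10% to 20%) | *m* = 1 (*a* = 10% to 20%) |
|---|---|---|---|
| 2% | 1.00 | 0.91 to 0.95 | 0.83 to 0.91 |
| 5% | 1.00 | 0.80 to 0.89 | 0.67 to 0.80 |
| 10% | 1.00 | 0.67 to 0.80 | 0.50 to 0.67 |

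At *m* = 0 this comparison is intact, and the error sits in whichever other category received the patients. If the item is left blank, the problem is lost data and possible selection, which this formula does not describe. The result therefore runs from no dilution to a halving, according to inputs that the documents do not give.

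**The case against.** The strongest reply is that the list is a parenthesis in a journal article and that the e-CRF is not shown. Articles do shorten option lists, and the form may hold a catch-all. This stands as a limit: one cannot say that patients *must* be miscoded or left missing, only that they would be if the printed list is the list in use. It does not remove the point, because the article sets out the options one by one and prints open categories for other items.

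The second reply is that no analysis named in the article is shown to be harmed. A reader might infer that the gap weakens a living-alone contrast in the SES analyses. The documents do not support that: no such contrast is defined, and the Discussion's examples of SES variables leave living conditions out. What remains is that section 2.5.1 collects the item for SES, so its reported distribution and any later use in research question (i) depend on it.

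A reader might also infer a definite attenuation. With 10% living alone at a hazard ratio of 1.5 and 5% unlisted at 1.0, a simple weighted average gives (10 × 1.5 + 5 × 1.0) / 15 = 1.33. All four inputs are assumed, and the sum puts every unlisted patient under living alone. That code is plainly untrue for someone living with parents or a carer, and a site could as easily choose a family code, in which case the contrast is not diluted at all.

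Nor do the documents support the idea that those affected are mainly younger and never married, or that they would drop out of complete-case models. They describe no such profile, and no missing-data method is stated.

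**Conclusion.** The concern holds in a limited form. As printed, the four options do not cover all eligible adults, and this follows from the text without any assumption. That records are affected rests on one condition: that the e-CRF carries the same four options. If it does, some patients have a wrong or blank value for an item collected to ascertain SES, possibly in a way that differs by center. The reported distribution of living conditions, and any SES analysis that uses it, would then be distorted.

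Direction and size cannot be given. They depend on how common unlisted households are and on which code sites chose, and the documents are silent on both. This is a minor, easily repaired flaw in one item and no threat to the registry as a whole.

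**What to change.** 1. Check the options in the live e-CRF. If a suitable one exists, the article's list only needs completing.
2. If none exists, add one option: *living with parents, siblings, other relatives or other persons (including a live-in carer)*. State that households of a partner plus such persons belong to it.
3. At the next planned visit or telephone contact, ask already registered patients whose household may be unlisted for their living situation **at enrollment**, and recode the baseline value. Select them whatever their current code or marital status. Re-asking only unmarried patients coded as alone or missing would overlook those placed under a family code and couples in shared households. Asking about the present would record status some 6 months late.

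The cost is one added option and one retrospective question. The answers will carry some recall error, and some early records may stay uncorrected, for example where a patient has died or cannot be reached. Doing this before the one-year baseline report keeps the number to be re-asked small.
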